## Abstract

**Background:**

Obesity represents a major public health problem and is the fifth leading risk factor for mortality. Morbid obesity is associated with chronic systemic inflammation which increases the risk of comorbidities. Bariatric surgery (BS) is considered an effective intervention for obese patients. However, BS is associated with dietary restriction, potentially limiting physical activity. Whole-body neuromuscular electrical stimulation (WBS) could represent an innovative option for the rehabilitation of BS patients, especially during the early postoperative phase when other conventional techniques are contraindicated. WBS is a safe and effective tool to combat sarcopenia and metabolic risk as well as increasing muscle mass, producing greater glucose uptake, and reducing the proinflammatory state. Therefore, the objective of this study is to evaluate the effects of WBS on body composition, functional capacity, muscle strength and endurance, insulin resistance, and pro- and anti-inflammatory circulating markers in obese patients undergoing BS.

**Methods/design:**

The present study is a randomized, double-blind, placebo-controlled, parallel groups clinical trial approved by the Ethics Committee of our Institution. Thirty-six volunteers (body mass index (BMI) > 35 kg/m^2^) between 18 and 45 years of age will be randomized to the WBS group (WBSG) or control (Sham) group (ShamG) after being submitted to BS. Preoperative assessments will include maximal and submaximal exercise testing, body composition, blood inflammatory markers, and quadriceps strength and endurance. The second day after discharge, body composition will be evaluated and a 6-min walk test (6MWT) will be performed. The WBS or Sham protocol will consist of 30 daily sessions for 6 consecutive weeks. Afterwards, the same assessments that were performed in the preoperative period will be repeated.

**Discussion:**

Considering the important role of WBS in skeletal muscle conditioning and its value as an aid in exercise performance, the proposed study will investigate this technique as a tool to promote early rehabilitation in these patients, and as a strategy to enhance exercise capacity, weight loss, and peripheral muscle strength with positive systemic effects. The present study is still ongoing, and data will be published after its conclusion.

**Trial registration:**

REBEC, RBR-99qw5h. Registered on 20 February 2015.

**Electronic supplementary material:**

The online version of this article (10.1186/s13063-018-2844-8) contains supplementary material, which is available to authorized users.

## Background

Obesity is a chronic disease that has reached epidemic proportions in children and adults; it is currently the fifth leading risk factor for mortality [1]. According to the World Health Organization (WHO), obesity has been growing at an alarming rate in the last decade and is becoming a significant public health problem [2, 3]. Obesity is a complex multifactorial disorder associated with derangements in immune function, low-grade inflammation, and changes in the amount of pro- and anti-inflammatory cytokines [4]. Adipose tissue is a metabolically dynamic, endocrine organ that participates in the regulation of physiological processes, including immunity-related processes, through the release of pro- and anti-inflammatory cytokines [4]. These include leptin, myostatin, adiponectin, and tumor necrosis factor (TNF)-α, all of which are involved in the development of cardiometabolic diseases, such as type II diabetes, and cardiovascular disease (CVD) [4].

Adipose tissue is recognized as an active tissue able to influence food intake control, energy balance, insulin action, lipids, glucose metabolism, angiogenesis, vascular remodeling, immunity, and inflammation [3, 4]. Obesity also leads to musculoskeletal dysfunction and reduces cardiorespiratory fitness as well as muscle strength, endurance, and flexibility. These effects often significantly contribute to chronic pain and functional limitations [5].

Many patients do not respond effectively to conservative therapeutic interventions for weight reduction and require a surgical approach, which is considered safe with a low mortality rate [6–8].

Conventional gastric bypass surgery, associated with dietary restriction in the postoperative (PO) period, limits physical activity performance and can lead to reductions in skeletal muscle mass and performance [9]. As such, strategies are needed to preserve and ideally enhance functional performance. In this context, whole-body neuromuscular electrical stimulation (WBS), which differs from conventional electrical stimulation, has been recently introduced as a strategy to simultaneously stimulate several large muscle groups. It represents a promising and innovative option to enhance weight loss, improve exercise capacity and peripheral muscle strength, and induce positive systemic effects [10–12]. Several studies have demonstrated that WBS reduces sarcopenia and abdominal fat mass in both young and older sedentary individuals [13]. These studies emphasize the potential effects of WBS—being able to act beneficially when other conventional exercises are contraindicated [13].

Another study showed that WBS could, through an increase in muscle mass, potentiate the action of insulin and thus produce greater uptake of glucose in the muscle as well as reduce the proinflammatory state. These findings may be particularly relevant in the obese population which is predisposed to greater insulin resistance [14].

While WBS may hold promise as a rehabilitation strategy following bariatric surgery (BS), especially in the early stages after surgery, there appears to be no evidence about its applicability in the bariatric PO period.

Therefore, the objective of this study is to evaluate the effects of WBS on body composition, functional capacity, muscle strength and endurance, insulin resistance, and pro- and anti-inflammatory circulating markers in obese patients undergoing BS in the early PO period.

We hypothesize that WBS would enhance functional capacity, muscle strength, and endurance, and reduce inflammation in BS patients when compared with controls (Sham). Moreover, we hypothesized that WBS would reduce fat mass, improve muscle mass, and positively affect insulin resistance and exercise capacity in these patients. We also expect patients to present good acceptance and adherence to the intervention protocol.

## Methods/design

### Study design

The present study is a randomized, double-blind, placebo-controlled, parallel groups clinical trial conducted at the Cardiopulmonary Physical Therapy Laboratory (LACAP) of the Federal University of São Carlos (UFSCar), São Carlos, SP, Brazil. This study was approved by the UFSCar Ethics Committee (number 966.613) and registered at the Brazilian Registry of Clinical Trials (ReBEC, RBR-99qw5h) on 20 February 2015. Recruited volunteers will all provide written informed consent prior to participation. The study will respect the Consolidated Standards of Reporting Trials (CONSORT) as show in the Fig. 1 with the template of content for the schedule of enrolment, interventions, and assessments. The study will also respect the Standard Protocol Items: Recommendations for Interventional Trials (SPIRIT) as shown in Additional file 1, respectively.

**Fig. 1 Fig1:**
[figure not shown]
Template of content for the schedule of enrolment, interventions, and assessments. T0: baseline variables; T1: preoperative evaluations; T2: allocation; T3: postoperative evaluation; T4: postintervention evaluation. 6MWT 6-min walking test, CPX symptom-limited or maximum cardiopulmonary exercise testing, WBS (Whole-body neuromuscular electrical stimulation)

### Volunteers

#### Recruitment, randomization, and blinding

Volunteers will be recruited from among patients included in a waiting list for BS and followed by a multidisciplinary team (composed of a physician, surgeon, anesthesiologist, cardiologist, physical therapist, nutritionist, and psychologist) for a minimum period of 1 year. During this period, volunteers will be counseled on smoking and alcohol cessation and informed about the surgical procedure and PO care.

Eligible volunteers will be evaluated within 1 month before BS, 2 days after discharge and, afterwards, will be randomized to the experimental or control group with a 1:1 allocation ratio by a computer-based permuted block randomization (www.randomization.com). To achieve a gender balance for both protocols, the randomization will be stratified by gender and two randomization plans for each gender will be proposed with blocks of 4. The randomization sequence will be generated by an independent research assistant and the intervention protocol will be applied by a physical therapist. Since the present study is a double-blind clinical trial, the volunteers, the physical therapist who will perform the assessments, and the researcher who will perform the statistical analysis will be blinded to the allocation of the volunteers.

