#### Inclusion and exclusion criteria

Inclusion criteria will be as follows: 1) body mass index (BMI) in class I (30–34.9 kg/m^2^), class II (BMI 35–39.9 kg/m^2^), or class III (BMI ≥ 40 kg/m^2^) obesity range for at least 3 years or more [15]. Patients with a BMI in the 30–34.9 kg/m^2^ range and presenting with associated comorbidities are candidates for BS at the discretion of medical staff and the endocrinologist [15]. Therefore, these patients will also be included in the present study); 2) no response to conventional and conservative treatment (pharmacological or not); 3) aged between 18 and 45 years; and 4) candidates for gastric bypass surgery.

Exclusion criteria will be as follows: 1) orthopedic conditions (arthrosis or pain) or neurological impairments that would preclude physical activity; 2) myocardial infarction within the last 6 months before study initiation; 3) implanted pacemaker or any metallic device; 4) unstable angina; 5) chronic heart rhythm disorders; 6) moderate or severe heart valve disease; 7) consistent history of heart disease; 8) uncontrolled hypertension; 9) uncontrolled and/or insulin-dependent diabetes mellitus; 10) β-blocker use; 11) chronic obstructive pulmonary disease (COPD) or other lung disorders; 12) any contraindication to the cardiopulmonary exercise test (CPX); 13) any health issues that compromise functional capacity testing; 14) distal arteriopathies; 15) any inflammatory, kidney, or liver conditions with documented diabetic neuropathy; 16) cognitive impairments or difficulty in comprehending or adhering to the procedures; 17) smoking; 18) use of drugs; 19) gestation; 20) use of psychotropic medications, anxiolytics, antidepressants, or appetite control medications; 21) postmenopausal women; and 22) concurrent participation in a regular exercise program. Patients with PO complications will also be excluded from this study.

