**Fig. 3 Fig3:**
[figure not shown]
Whole-body electrical stimulation exercises performed by a recruited volunteer

The sessions will last approximately 20–30 min using a previously described protocol, involving a rectangular wave by a symmetrical bipolar electric pulse [13]. Considering a total of 6 weeks of training for both groups, the WBS protocol will be performed in three nonconsecutive days of endurance alternating with 2 days of training per week. All sessions will occur with the supervision of a trained physical therapist.

The endurance training session will apply a bipolar electrical current with a frequency of 85 Hz and an impulse breadth of 350 μs intermittently with 6 s of electrical stimulation using a direct impulse boost to perform the exercise and 4 s off for rest, with ramp of 0.4 s. The total time under current per session will be approximately 12 min, with approximately 5 min of rest between sets. The strength sessions will consist of the same bipolar electrical current, with a frequency of 30 Hz and impulse breadth of 350 μs intermittently, 4 s of electrical stimulation and 10 s of rest, with ramp of 0.4 s. These sessions will last approximately 8 min, with approximately 5 min of resting between exercises.

The intensity of both sessions is prescribed to reach submaximal levels, which will be adjusted to each region according to disparities of current sensitivity, respecting visual and effective contraction, without volunteer discomfort [30, 31]. To maintain an adequate and tolerable exercise intensity, the BORG scale was used. Thus, volunteers should score between 2 and 3 for the perception of effort in this scale in the endurance protocol and above 5 in the protocol of force [31, 32].

The difference between the WBS and control intervention is that the intensity of electrical stimulation will be switched off in the latter group to avoid any influence of WBS equipment during the exercises. Volunteers will be instructed not to perform any regular exercise activities, being questioned weekly with respect to compliance with these recommendations. After the postintervention assessment, the WBS protocol will be offered to the control group.

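### Fixed, published blocks of 4 within gender at one laboratory make about 30–33% of allocations deducible by anyone who knows the earlier ones; this is an avoidable vulnerability, not demonstrated bias

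*Protocol article*

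**What the plan says.** All references are to the Protocol article.

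- Recruitment, randomization, and blinding: patients are allocated "with a 1:1 allocation ratio by a computer-based permuted block randomization", and "the randomization will be stratified by gender and two randomization plans for each gender will be proposed with blocks of 4". No variation in block size is mentioned.
- Study design: the trial is conducted at a single laboratory.
- Recruitment, randomization, and blinding, on roles: "The randomization sequence will be generated by an independent research assistant and the intervention protocol will be applied by a physical therapist". The blinded roles are the volunteers, the assessing therapist and the analyst. The treating therapist is not among them.
- Intervention protocol: a therapist supervises every session, and in the control arm "the intensity of electrical stimulation will be switched off in the latter group". Whoever runs the sessions therefore learns each patient's arm.
- Inclusion and exclusion criteria: "Patients with PO complications will also be excluded from this study". No decision-maker or time limit is given.
- Recruitment, Postoperative data collection and Intervention protocol all place randomisation after the postoperative assessment. The Fig. 1 legend numbers allocation as T2 and the postoperative evaluation as T3, which is the reverse order.
- Trial status: recruitment is under way.

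**The concern.** A permuted block of known size gives away its last places to anyone who has seen the first ones. Three features come together here: the size is fixed and published, there are only two strata at one site, and at least one member of staff knows every allocation already made. The last eligibility decision, exclusion for postoperative complications, falls close to randomisation.

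If the person making that decision could work out the next allocation, the decision could depend on it, and the two arms would no longer be comparable in the way randomisation is meant to secure. Having an independent person generate the sequence, or concealing each assignment until use, does not close this route. The deduction uses only past allocations and the block size.

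**Working it through.** The plan gives no figure for predictability. The only plan figure used is the total of 36, taken as stated. For reference, 2 × 16 = 32, and 32/0.85 = 37.6, rounded up to 38, which is within two patients of 36. Nothing below depends on that difference.

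**Inputs.** Block size 4, ratio 1:1, one list per gender (Recruitment, randomization, and blinding); 36 patients (Sample size). Assumption: the observer knows the block size and all earlier allocations in that list.

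**One complete block.** There are 6 equally likely orders of two A and two B.

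| Position | Certain in advance | Best guess right |
|---|---|---|
| 1 | 0 | 1/2 |
| 2 | 0 | 2/3 |
| 3 | 1/3 (first two alike: AABB, BBAA) | 1/3 × 1 + 2/3 × 1/2 = 2/3 |
| 4 | 1 | 1 |

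- Certain: (1/3 + 1)/4 = 33.3%.
- Best guess right: (1/2 + 2/3 + 2/3 + 1)/4 = 17/24 = 70.8%.

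**All 36 patients.** The gender split is not given. Since 36 is a multiple of 4, only three cases arise with one list per gender:

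- Both genders a multiple of 4 (for example 24/12): 9 complete blocks, 9 × 4/3 = 12.0 certain.
- Remainders 3 and 1 (for example 27/9): 8 × 4/3 + 1/3 = 11.0 certain.
- Remainders 2 and 2 (for example 18/18): 8 × 4/3 = 10.7 certain, and 10.7/36 = 29.6%.

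The expected number is therefore 10.7 to 12.0 of 36, or 30–33%.

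**Two lists per gender.** If the wording on plans is read as two lists for each gender, and the observer knows which list is in use, the expected number certain is 9.3 to 10.7 for splits from 18/18 to 32/4. That reading lowers predictability slightly.

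**Effect of varying the block size.** Simulation with 18 patients per list, sizes drawn with equal probability, 20,000 repetitions, and an observer who knows the possible sizes and all earlier allocations:

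| Block sizes | Certain | Best guess right |
|---|---|---|
| 4 (as planned) | 29.7% | 69.4% |
| 4, 6 | 5.9% | 68.4% |
| 2, 4, 6 | 3.7% | 69.6% |
| 4, 6, 8 | 2.3% | 67.0% |

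The first row agrees with exact arithmetic: 4 × 4/3 = 5.33 certain, and 5.33/18 = 29.6%. Varying the size removes most of the certain allocations. It hardly changes the best-guess rate.

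**The case against.** The strongest reply is that the route to bias is not in the document. The article separates the roles: an independent assistant generates the sequence, one therapist treats, and the assessor is blinded. Nowhere does it say that the treating therapist enrols patients or judges complications. Concealment details may stand in the full protocol, which is not shown. Blocks of 4 are also a common and defensible choice when balance within gender matters in 36 patients. All of this stands, and it limits the point to a vulnerability. It does not remove the point, because the fixed size is something the article itself sets and publishes.

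Four stronger readings may tempt a reader, and the documents do not support them:

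- *Encouragement at the postoperative 6MWT is affected.* This would need an assessor who knows earlier allocations, and the article states that the assessor is blinded.
- *The phrase "two randomization plans for each gender will be proposed with blocks of 4" makes matters worse.* It may simply mean one plan for each gender. Even two lists per gender would slightly lower predictability. No choice of list for individual patients is described. The wording needs tidying but is not an aggravating fact.
- *Best-guess success of 71% against 50% by chance measures the harm.* Every blocked scheme checked above stays at about 67–70%, so this contrast overstates what a change of block size can achieve.
- *Allocation is released before the postoperative assessment.* Only the Fig. 1 legend suggests this. Three sections of text give the opposite order, so it is a conflict to resolve and not evidence of practice.

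**Conclusion.** The point holds as an avoidable weakness in the allocation scheme. An observer with full knowledge of earlier allocations in a gender list could deduce 30–33% of allocations with certainty (10.7 to 12 of 36). The first two places of each block are never certain. The figure assumes one list per gender, a known block size and complete knowledge of past allocations. The lower end applies to an 18/18 split, and 12 is the maximum.

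No bias in the primary outcome is shown. It would require knowledge of earlier allocations to reach whoever decides on exclusion for postoperative complications, and the article does not say who that is or what that person knows. Changing the block size is a cheap improvement and not the correction of an error. The order of allocation and postoperative evaluation in the Fig. 1 legend is a separate inconsistency that needs correcting.

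**What to change.** For patients not yet randomised:

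1. Generate one list per gender with randomly varied block sizes (for example 4 and 6, or 2, 4 and 6), and do not disclose the sizes to treating or assessing staff.
2. Record the decision on postoperative complications, with date and time, before the allocation is released. The text already places the postoperative assessment before randomisation, so the dated record is the only new step.
3. Reword the sentence on plans to state one list per gender.
4. Reconcile the T2/T3 order in the Fig. 1 legend with Recruitment, randomization, and blinding, Postoperative data collection, and Intervention protocol.

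The cost is regenerating the remaining sequence and keeping one dated entry per patient, with no added staff or patients. The statistical price is a possible imbalance of up to 3 in an unfinished block of 6 per gender, against 2 in an unfinished block of 4. Because the best-guess rate barely moves, non-disclosure and the recorded decision are as much a part of the remedy as the varied sizes.

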#### Inclusion and exclusion criteria

Inclusion criteria will be as follows: 1) body mass index (BMI) in class I (30–34.9 kg/m^2^), class II (BMI 35–39.9 kg/m^2^), or class III (BMI ≥ 40 kg/m^2^) obesity range for at least 3 years or more [15]. Patients with a BMI in the 30–34.9 kg/m^2^ range and presenting with associated comorbidities are candidates for BS at the discretion of medical staff and the endocrinologist [15]. Therefore, these patients will also be included in the present study); 2) no response to conventional and conservative treatment (pharmacological or not); 3) aged between 18 and 45 years; and 4) candidates for gastric bypass surgery.

Exclusion criteria will be as follows: 1) orthopedic conditions (arthrosis or pain) or neurological impairments that would preclude physical activity; 2) myocardial infarction within the last 6 months before study initiation; 3) implanted pacemaker or any metallic device; 4) unstable angina; 5) chronic heart rhythm disorders; 6) moderate or severe heart valve disease; 7) consistent history of heart disease; 8) uncontrolled hypertension; 9) uncontrolled and/or insulin-dependent diabetes mellitus; 10) β-blocker use; 11) chronic obstructive pulmonary disease (COPD) or other lung disorders; 12) any contraindication to the cardiopulmonary exercise test (CPX); 13) any health issues that compromise functional capacity testing; 14) distal arteriopathies; 15) any inflammatory, kidney, or liver conditions with documented diabetic neuropathy; 16) cognitive impairments or difficulty in comprehending or adhering to the procedures; 17) smoking; 18) use of drugs; 19) gestation; 20) use of psychotropic medications, anxiolytics, antidepressants, or appetite control medications; 21) postmenopausal women; and 22) concurrent participation in a regular exercise program. Patients with PO complications will also be excluded from this study.

#### Sample size

The sample size calculation was performed using GPower, Version 3.1.3 (Franz Faul Universität Kiel, Germany), based on a previous study by our group performed on BS patients [16] which showed a difference between the distance walked during a 6-min walking test (6MWT) before and after aerobic training of 49.7 ± 15 m. We hypothesize that we will see an improvement in 6MWT distance following WBS to a similar level as our previous study. Therefore, we projected a sample size that would provide 80% power at a significance level of α = 0.05, detecting a variation of 30% as a favorable outcome. These parameters indicate a sample of five volunteers would be required to investigate functional gains after the intervention.

The primary outcome measure for the study will be the 6MWT distance in meters since the distance walked following interventions in patients with chronic conditions is an important tool to assess the efficacy of interventions that theoretically improve functional capacity [16]. Secondary outcomes of this study are to investigate whether the intervention prevents muscle mass loss and whether there is an association between 6MWT distance with lean mass in kilograms [17]. Therefore, since the performance improvement, the prevention of lean mass loss, and the association between these measures represent important outcomes in the present study, the sample size was recalculated. Based on the bivariate normal correlation model, considering a significance level of 5%, a sample power of 95%, and a strong correlation (> 0.70) between lean mass percentage and 6MWT performance as the main outcome, the calculated sample size was 16 volunteers per group. Anticipating a dropout rate of approximately 15%, a total of 36 patients will be included in the present study.

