### Intervention protocol (WBS or sham protocol)

Following the PO assessments and subsequent randomization, the volunteers will return to the laboratory to perform the intervention protocol with WBS equipment (Miha Bodytec, Augsburg, Germany) [29] as described in other studies [30–32]. The experimental group (WBSG; *n* = 16) will perform the WBS protocol while the control group (ShamG; *n* = 16) will perform the same protocol without WBS stimulus.

The WBS vests and cuff electrodes allow for simultaneous control and innervation of 14–18 muscle groups or 10 regions (upper legs, upper arms, bottom, abdomen, chest, lower back, upper back, including the latissimus dorsi) with a selectable intensity for each one allowing a total electrode area of up to 2800 cm^2^ [32, 33]. The strain and current intensity can be individually selected and modified during the protocol and be progressively increased during each training session. The parameters will be saved on smart cards to ensure reliable and valid application during the WBS protocol [31, 32].

WBS stimulation will be accompanied by low-intensity movements to allow an effective contraction (maximum voluntary contraction requested by the supervisor) during electrical stimulation. The exercises will be carried out without any additional weights with volunteers in the standing position. Specifically, WBS will be performed in conjunction with 10–14 dynamics: squat, trunk flexion, exercises of upper limbs, and isometric abdomen contraction. In the experimental group, these muscle contractions will be performed simultaneously with an electrical stimulation current. Figure 3 illustrates a volunteer performing the protocol with a WBS vest.

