### Statistical analysis

A blinded researcher will perform all statistical analyses for this study. The volunteers will be codified by the researcher responsible for randomization to ensure blinding of control and intervention groups. Descriptive statistics including the mean, standard deviation (SD), and quartiles will be applied to summarize the data. The Shapiro Wilk test will be used to investigate data distribution. Data will be expressed as mean, SD, and 95% confidence interval. The primary analysis is to assess the effect of the intervention on 6MWT distance and the secondary analysis is the relationship between 6MWT distance and the lean mass loss.

In this sense, the effect of WBS will be assessed in the context of the following hypotheses:H0: WBS does not improve 6MWT distance and/or does not prevent the loss of muscle mass.H1: WBS increases 6MWT distance and/or prevents the loss of muscle mass.

If the data present a normal distribution, analysis of variance (ANOVA) will be tested for comparisons between the body composition and 6MWT distance change considering three periods of evaluation (preoperative, postoperative, and postintervention). In instances where data are not normally distributed, nonparametric tests will be applied.

The benefits obtained by both groups will be demonstrated through the difference between postintervention results minus PO data with all variables that will be collected. Comparisons between groups will be assessed using the unpaired Student *t* test or Mann-Whitney test, as appropriate.

Effect size will be analyzed using Cohen’s *d*, and the results will be interpreted based on the Cohen classification [34] as follows: small (0.21–0.49), medium (0.50–0.79), or large (> 0.80).

The statistical analysis using correlation will assess the degree of association (or dependence) between improvements in functional tests, body composition data (InBody 720 and DXA), muscular assessment (dynamometry), and concentration of cytokines.

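### The sample-size section gives no power for the primary comparison, WBS versus sham on 6MWT distance: its 80% belongs to a one-group change and its 95% to a secondary correlation

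*Protocol article*

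**What the plan says.** All references are to the protocol article.

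- **Sample size, first calculation.** The input is an earlier study by the same group in bariatric patients, which "showed a difference between the distance walked during a 6-min walking test (6MWT) before and after aerobic training of 49.7 ± 15 m". The expectation for this trial is put as follows: "We hypothesize that we will see an improvement in 6MWT distance following WBS to a similar level as our previous study". The target is "80% power at a significance level of α = 0.05, detecting a variation of 30% as a favorable outcome", and the result is "These parameters indicate a sample of five volunteers would be required to investigate functional gains after the intervention". No change in the sham arm and no WBS-minus-sham difference is given.
- **Sample size, second calculation.** 6MWT distance is named as the primary outcome; lean mass loss and its association with 6MWT distance are secondary. The size is then recalculated from a bivariate normal correlation model at 5% significance and 95% power, assuming "a strong correlation (> 0.70) between lean mass percentage and 6MWT performance as the main outcome". This gives 16 per group, and 36 in total after allowing for about 15% dropout.
- **Intervention protocol.** The sham arm "will perform the same protocol without WBS stimulus".
- **Statistical analysis.** The effect of the intervention on 6MWT distance is the primary analysis, and its relationship with lean mass loss is secondary. Benefit is measured as the postintervention value minus the postoperative (PO) value. "Comparisons between groups will be assessed using the unpaired Student" t test, or Mann-Whitney.

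**The concern.** The primary question is a difference between two randomised arms. Its power depends on the expected WBS-minus-sham difference in 6MWT change, the SD of that change, and the number per arm. The section supplies only the last of these, and takes it from a calculation for something else.

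A one-group change cannot simply stand in for the net difference here. Sham patients do the same supervised exercises without current for six weeks, and they recover from the same operation over the same period. Some improvement in that arm is plausible, but the document does not say how much.

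A correlation calculation gives a number of paired observations in a sample. Its 95% power carries no information about a difference between arms.

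The stake is interpretation. If the 6MWT comparison shows no difference, a reader looking for the planned power will find 80% and 95%, and neither applies to that comparison.

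**Working it through.** **Inputs from the Sample size section:** change 49.7 m; 15 m, taken here as the SD of change (an assumption, since the text does not say what the ± figure is); power 80%; α = 0.05, taken as two-sided (sidedness is not stated); 16 per group; 36 in total; 15% dropout.

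**Formulas.** Noncentral t with d = difference / SD. Paired test: noncentrality d√n, n − 1 degrees of freedom. Two-sample test: noncentrality d√(n/2), 2n − 2 degrees of freedom, with n per group.

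**Step 1: the five volunteers.** The 30% can be read in three ways:

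- full effect: 49.7 m, d = 49.7/15 = 3.31
- effect reduced by 30%: 0.7 × 49.7 = 34.8 m, d = 2.32
- 30% of the effect: 0.3 × 49.7 = 14.9 m, d = 0.99

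| Effect | First n with 80%, paired | Power at n = 5, paired | First n per group with 80% | Power at 5 per group |
|---|---|---|---|---|
| 49.7 m | 3 (81%) | 99.9% | 3 (85%) | 99.5% |
| 34.8 m | 4 (86%) | 97% | 5 (89%) | 89% |
| 14.9 m | 11 (84%) | 40% | 17 (80%) | 28% |

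Five is the exact answer in one cell only: a two-sample test, per group, with the effect reduced by 30% (four per group gives 78%). The text mentions neither a per-group count nor a reduced effect. Under the full effect five is more than needed; under 14.9 m it falls well short. On every reading the input is a within-group change.

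**Step 2: the 16 per group.** With a correlation of 0.70 and 95% power, the exact bivariate-normal calculation needs 17 one-sided (power at 16 is 94.5%) or 20 two-sided (power at 16 is 90%). The 16 is therefore close to the one-sided answer. Either way it is a number of pairs for a test of correlation.

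**Step 3: evaluable patients.** 36 × 0.85 = 30.6, or about 15 per group. The plan's own evaluable figure is 16.

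**Step 4: power of the unpaired comparison, two-sided 5%.**

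| Net difference | SD 15 m: 15 / 16 per group | SD 30 m: 15 / 16 per group |
|---|---|---|
| 14.9 m | 75% / 78% | 26% / 28% |
| 34.8 m | >99% / >99% | 87% / 89% |
| 49.7 m | >99% / >99% | 99% / >99% |

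**Step 5: detectable difference at 80% power.** The standardised difference is 1.06 with 15 per group and 1.02 with 16. Multiplied by the SD:

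- SD 15 m: 15.9 and 15.4 m
- SD 30 m: 31.8 and 30.7 m
- SD 50 m: 53.0 and 51.2 m

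The SDs of 30 and 50 m are assumptions chosen to show the range.

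**The case against.** Four points can be made for the plan.

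- **The trial may be amply powered.** The section expects an improvement similar to the earlier study. If most of the 49.7 m were net of sham and the SD were 15 m, 16 per group would have power above 99%. This stands. A reader might infer that the trial is underpowered, or that it lacks a power it claims. The document supports neither: it never claims 80% or 95% for WBS versus sham, and low power appears only when the smallest reading of the effect is used with five volunteers or with a larger, assumed SD.
- **Five volunteers can be recovered.** It matches a two-sample calculation with the effect reduced by 30%. This also stands, so the 40% and 28% figures hold under one reading and do not prove an arithmetical error. What remains is that the text does not say which reading was used.
- **The main-outcome phrase may be only loose.** In "a strong correlation (> 0.70) between lean mass percentage and 6MWT performance as the main outcome", the last words could attach to 6MWT performance, which is the named primary outcome. That is a possible reading, so a flat contradiction is not established. The calculation still concerns the correlation.
- **Taking the larger of two sizes does no harm.** True for the number recruited. It does not turn the 95% into power for the treatment comparison.

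**Conclusion.** The point holds as a gap in the justification of the sample size. The protocol states no power for its primary between-arm comparison: the 80% rests on a one-group change with an ambiguous 30%, and the 95% on an association that the protocol itself makes secondary.

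The consequence for the trial cannot be fixed at one number, because the document gives neither a WBS-minus-sham difference nor an SD of change identified as such. With about 15–16 evaluable per group, the design detects a standardised difference of about 1.02–1.06 with 80% power. Whether that is adequate depends on the net effect expected after sham exercise and surgical recovery, and on the SD. These results assume a two-sided 5% unpaired t test with equal SDs in the two arms.

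Randomisation, the outcome, the planned test and the validity of the treatment estimate are unaffected.

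**What to change.** Keep 36 patients and rewrite the Sample size section:

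1. Remove the five-volunteer statement, or label it as a within-group calculation and say what the 30% means.
2. State the WBS-minus-sham difference in 6MWT change (postintervention minus PO) that the trial seeks to detect, and why.
3. Give the power of the unpaired comparison at about 15–16 evaluable per group over a range of SDs, each labelled as an assumption, including 15 m. Possible wording: with 36 randomised and about 15–16 per group evaluable, a two-sided 5% unpaired test has 80% power for a standardised difference of about 1.02–1.06, that is 15–16 m if the SD of change is 15 m, 31–32 m if 30 m and 51–53 m if 50 m.
4. Label the correlation calculation as secondary, and reword the phrase that calls it, or 6MWT performance, the main outcome.

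The cost is protocol wording only; no patients or procedures are added. The downside is that the stated power will look less favourable than the present 80% and 95%.
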